### **Cohort B:**

- Identify tetramers that can be used to measure specific memory subpopulations in PBMC pre-exposure to measles;
- Measure and characterize MV-specific cellular immune responses in PBMC;
- Measure MV-specific antibody concentrations in plasma samples;
- Measure diagnostic haematological parameters, including numbers (and differentiation) of white blood cells, red blood cells, platelets;
- Measure expansion and/or depletion of lymphocyte subpopulations in relation to MV infection, by T-cell receptor rearrangement studies;

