**Cohort B:**

To obtain significant data in cohort B, we require paired pre- and post-measles PBMC of at least 50 children. This will allow statistical comparison of the precursor frequencies of circulating memory lymphocyte populations before and after measles.

Here, we need to take other uncertainties into account. Most importantly, it is a possibility that children that consent to collection of a pre-measles blood sample may decide to withdraw their consent for collection of a second sample. Historically, it has been observed that this occurs in approximately 50% of the children. An additional theoretical risk is that the school of the children does not become involved in the measles outbreak. However, observations from previous measles outbreaks in the bible belt suggest that this risk is low, especially since we intend to recruit children at schools with very low vaccination coverage. Finally, the detection of memory lymphocyte populations by flow cytometry will determine on the availability of suitable tetramers that can be used to stain these populations by flow cytometry. Tetramers are restricted to specific HLA-haplotypes, and thus technical limitations may result in the inability to detect memory lymphocytes in a specific patient.

As a result, we estimate that it will be necessary to collect a first blood sample of 100 children.

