#### 5.1.2 Secondary study parameters/endpoints (if applicable)

**Cohort A:** secondary study parameters in cohort A are the identification and characterization of cell-free and cell-associated virus, both in terms of quantity (what virus concentrations are present in the upper respiratory tract in relation to transmissibility of MV) and quality (what does transmissible MV look like under the electron microscope?). In addition, we will investigate what cytokines, chemokines and acute phase proteins can be measured in the plasma during the early stage of acute MV infection, in relation to the level of lymphopenia (reduced lymphocyte numbers in peripheral blood).

**Cohort B:** secondary parameters in cohort B are the measurement and characterization of MV-specific humoral and cellular immune responses. Massive expansion of MV-specific (and bystander) B- and T-lymphocyte populations is an essential characteristic of our immune suppression model, so we will investigate whether the quantitative and qualitative composition of the circulating lymphocyte pool of children after measles has indeed changed when compared to the pre-infection sample, while the composition of the paired samples of the control children remains essentially unaltered.

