## 6.2 Secondary study parameter(s)

**Cohort A:** secondary study parameters in cohort A are the identification and characterization of cell-free and cell-associated virus, both in terms of quantity (what virus concentrations are present in the upper respiratory tract in relation to transmissibility of MV) and quality (what does transmissible MV look like under the electron microscope?). In addition, we will investigate what cytokines, chemokines and acute phase proteins can be measured in the plasma during the early stage of acute MV infection, in relation to the level of lymphopenia (reduced lymphocyte numbers in peripheral blood). These data will be described qualitatively, and do not require statistical analysis.

**Cohort B:** secondary parameters in cohort B are the measurement and characterization of MV-specific humoral and cellular immune responses. Massive expansion of MV-specific (and bystander) B- and T-lymphocyte populations is an essential characteristic of our immune suppression model; we will explore different methods to demonstrate that the qualitative composition of the circulating lymphocyte pool of children after measles is dramatically altered as compared to the pre-infection sample. If successful, these data will be analysed using a similar approach as above: by paired t-test on log-transformed data or by Mann-Whitney U-test if data are not normally distributed.

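### Section 6.2 lets the cohort B secondary analysis depend on seeing the hypothesised change: the methods are open, the aim is to show an alteration, and testing follows only on an undefined success

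*Protocol*

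**What the plan says.** The protocol describes this parameter in three places.

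- **Objectives, Cohort B.** One bullet in the list of secondary studies reads "Measure expansion and/or depletion of lymphocyte subpopulations in relation to MV infection, by T-cell receptor rearrangement studies". It is neutral about direction and names an assay. Other bullets in that list cover measles-specific cellular responses, antibodies and haematology.
- **Section 5.1.2, Cohort B.** The endpoint is put as a question: "we will investigate whether the quantitative and qualitative composition of the circulating lymphocyte pool of children after measles has indeed changed" relative to the pre-infection sample. It is set against a comparator: "while the composition of the paired samples of the control children remains essentially unaltered".
- **Section 6.2, Cohort B.** The analysis section says "we will explore different methods to demonstrate that the qualitative composition of the circulating lymphocyte pool of children after measles is dramatically altered" as compared with the pre-infection sample. It continues "If successful, these data will be analysed using a similar approach as above", namely "by paired t-test on log-transformed data or by Mann-Whitney U-test if data are not normally distributed".

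Section 6.2 does not give the number, list or order of the methods. It does not say what makes a method successful, or when that is judged relative to the pre/post comparison.

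**The concern.** Between sections 5.1.2 and 6.2 an open question becomes a conclusion to be shown, and the formal test is placed behind a condition. The only aim stated before that condition is to show the alteration. The literal reading is therefore that a method counts as successful when it shows the expected change, and that only then are its data tested. A measurement method would be admitted to the analysis on the strength of the outcome it is meant to assess.

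The protocol treats expansion of measles-specific and bystander lymphocytes as essential to its model of immune suppression, so a finding of no change would count against the model. A test applied only to methods already seen to show the change can neither confirm nor refute that part of the model, and its p-value does not have its nominal error rate.

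**Working it through.** **The passages side by side**

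| Feature | Section 5.1.2 | Section 6.2 |
|---|---|---|
| Question | Whether composition changed | To show that it is dramatically altered |
| Scope | Quantitative and qualitative | Qualitative only |
| Control children | Named as comparator | Not mentioned |
| Methods | Not named here; one assay in the objectives | Different methods, unspecified |
| Condition for testing | None | Success, undefined |

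The primary cohort B analysis in section 6 makes a useful contrast. It also has an entry condition: data count only if memory populations can be identified in the pre-exposure sample. That condition uses the first sample alone, so it cannot depend on the pre/post change. Section 6.2 has no equivalent safeguard.

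**Inputs for the illustration**

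- Pairs: n = 50, from section 1.4 ("we require paired pre- and post-measles PBMC of at least 50 children"). The protocol's own figure reproduces: 50 pairs with about 50% loss of second samples needs 50 / (1 − 0.5) = 100 first samples, as stated. That figure is not in dispute.
- Number of methods k: not given. Assumed values 3, 5 and 10.
- Significance level: not given. Assumed two-sided 0.05 per method.
- Correlation between methods applied to the same pairs: not given. Assumed values 0, 0.5 and 0.8.

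**Independent methods, no true change**

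P(at least one of k significant) = 1 − (1 − 0.05)^k

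- k = 3: 1 − 0.95³ = 0.143
- k = 5: 1 − 0.95⁵ = 0.226
- k = 10: 1 − 0.95¹⁰ = 0.401

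**Correlated methods, no true change**

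These come from simulating k equally correlated paired differences with 50 pairs, each tested by a paired t-test, in 20,000 runs. As a check, the simulation gives 0.050 to 0.051 for a single method, and 0.140, 0.226 and 0.404 for k = 3, 5 and 10 at zero correlation, in line with the formula.

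| k | Correlation 0 (formula) | 0.5 | 0.8 |
|---|---|---|---|
| 3 | 0.143 | 0.125 | 0.099 |
| 5 | 0.226 | 0.179 | 0.125 |
| 10 | 0.401 | 0.292 | 0.178 |

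**With the selection removed**

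One method named in advance keeps the nominal 0.05. If k methods were each tested at 0.05/k, the chance of any false positive would be 1 − (1 − 0.05/k)^k, which is 0.0492 for k = 3 and 0.0490 for k = 5 under independence.

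**What the figures cover**

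They describe picking the best of k methods. Under the strictest literal reading the problem is of another kind. If success is judged by the same pre/post difference that the test then examines, the tested results favour the hypothesis by construction, whatever k is.

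**The case against.** **A technical reading of success is natural.** The test comes after the condition, and testing a change already shown would be redundant. The protocol treats cohort B assays as technically uncertain elsewhere: section 1.4 notes that tetramers depend on HLA type and may fail in some children. This stands as a possible reading, but it is not the one written. The protocol could close the gap by saying it.

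**No search until success is stated.** A reader might infer that methods will be tried one after another until one shows a dramatic change, that those showing none go unreported, and that a positive result is therefore built in. The protocol does not say this. It describes no sequence and no stopping on success. Sections 8.5 and 8.6 promise a final report and adherence to a publication policy. Neither section commits to reporting every method tried, but neither allows a method to be suppressed.

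**The endpoint is already neutral in section 5.1.2, and the parameter is secondary.** Both are true. The main cohort B hypothesis rests on tetramer frequencies and is untouched. The verb *explore* suggests an exploratory purpose, yet section 6.2 plans formal tests without labelling them exploratory.

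**Detail of this kind belongs in a statistical analysis plan.** That holds for the list of assays and for multiplicity, and their absence is not the point here. The point is a conditional rule that the protocol does state, in terms that depart from its own endpoint section.

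**T-cell receptor rearrangement cannot be the sole measure.** This stands in full. Section 6.2 concerns B- as well as T-lymphocytes, and the objectives do not present rearrangement as the only method.

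**Conclusion.** The concern holds as a fault of wording that has a statistical consequence. Section 6.2 states an aim of showing a preset result with unspecified methods and makes testing conditional on a success that, read literally, is the result itself. It thereby permits methods to be selected by outcome and departs from the neutral question in section 5.1.2. It does not guarantee a positive finding, because success may also mean a workable assay.

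If the best of k methods were picked, the false-positive chance would be about 14% (k = 3) or 23% (k = 5) for independent methods, and about 10% or 12% at correlation 0.8, against a nominal 5%. These figures rest on an assumed number of methods, an assumed two-sided 5% level per method and assumed correlations. Methods run on the same samples are likely to be correlated, so the independent figures are better read as the upper end. The effect is confined to this secondary parameter.

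**What to change.** Reword the cohort B paragraph of section 6.2:

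1. State the aim as in section 5.1.2: to investigate *whether* composition changed, with the control children as comparator.
2. Replace the success condition with a technical-validity criterion, for example adequate cell numbers and passed assay controls, judged before pre- and post-measles values are compared.
3. Commit to analysing and reporting every technically valid method in all available pairs, including methods that show no change.
4. Label these analyses exploratory.
5. List T-cell receptor rearrangement, already named in the objectives ("by T-cell receptor rearrangement studies"), as one planned method and not the only one, since B cells are also in scope.

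The change needs no extra children or blood samples. The cost is that methods showing no change must also be analysed and reported, and that technical validity has to be recorded before the comparison is made.

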## 6.3 Other study parameters

Not applicable

## 6.4 Interim analysis (if applicable)

Not applicable

## **7. ETHICAL CONSIDERATIONS**

### **7.1 Regulation statement**

The study will be conducted according to the principles of the Declaration of Helsinki, as amended by the 59th WMA General Assembly, Seoul, Korea, October 2008, and in accordance with the Medical Research Involving Human Subjects Act (WMO) and other guidelines, regulations and Acts.

### **7.2 Recruitment and consent**

#### **Cohort A:**

Measles is a notifiable disease and will be notified to the infectious disease specialists of the Municipal health Service. Municipal Health infectiologists residing in the Bible Belt area often have contacts in the orthodox Protestant community already. They will contact parents and ask them if they are interested to participate in the study. In addition, we will also inform orthodox Protestant General Practitioners of our research plans, by using our a page information sheet. If parents are potentially interested in allowing their children to participate in the study, we will provide them with our Letter of Consent. In this letter we ask them to decide within three days whether or not their children can participate, because the window of opportunity to collect samples during the incubation phase of the disease is relatively short. As soon as parents indicate they consent to the study we will visit them at home, and answer any additional questions they may have. After the parents (and potentially the children, if aged above 11) have signed the consent forms, we will collect the clinical specimens.

#### **Cohort B:**

In order to recruit subjects to cohort B, we intend to approach schools with low vaccination coverage (<30%) that have not yet seen measles cases in their school. We expect that measles will spread rapidly to all children in the school once the virus is introduced. Municipal Health infectiologists often have existing relationships with these schools, and can suggest which schools to approach. If the head of the school is convinced of the potential usefulness of the study, we will ask his permission to distribute the one page information sheet and the Informed Consent amongst children at the school. Parents who are willing to participate will fill in their contact information on the information sheet, which will be returned at the school and subsequently be collected by the research team. If the head of the school or the parents would consider this useful, we will try to organise an information session at the school, during which we can provide more background information about the virus, the disease and our clinical study. Parents who indicate they are willing to consent to the study will first be contacted by telephone, and subsequently be visited at home, and we will answer any additional questions they may have. After the parents (and potentially the children, if aged above 11) have signed the consent forms, we will collect the clinical specimens. Subsequently, the course of the

measles outbreak at the school will be monitored by the Municipal Health office. As soon as the outbreak at the school appears to be finished, we will start making arrangements for collection of the second blood sample. To this end, the children will again be visited at their home address. If the school and parents indicate they would prefer blood collection to take place at another location, we will investigate whether we can organize this either at the school or at a regional Municipal Health-associated location.

### **7.3 Objection by minors or incapacitated subjects (if applicable)**

The informed consent letters will need to be signed by both parents. If the participating children are aged above 11, they will also need to sign themselves. However, even if parents have signed the informed consent letter, children who clearly indicate they do not want the clinical specimens to be collected will not be included in the study. We will strictly adhere to the 'Code of conduct relating to expressions of objection by minors participating in medical research' as established by the Netherlands Association for Paediatric Medicine (NVK) on 21 May 2001 and published in NVK Newsletter no. 3, June 2001.

### **7.4 Benefits and risks assessment, group relatedness**

The study does not result in benefits to the participating children. However, the risks are minimal and the study can only be performed in this age group and this community due to the fact that the vast majority of individuals aged 14 and over in the Netherlands are immune to measles, either due to previous natural infection or vaccination. The bible belt population constitutes a unique community in the world, as previous outbreaks of infectious diseases, including measles, have been well documented. Based on these observations, we can be certain that all unvaccinated children in the orthodox Protestant community that live in this geographic region and go to schools with low vaccination grade will be infected with measles virus during this outbreak. In addition, the relatively large family size in orthodox Protestant families increase the chances of identifying families in which one child has already been diagnosed with measles, while his or her siblings are still in the incubation phase of measles virus infection. Together, the ongoing measles outbreak in the orthodox Protestant community provides us with a unique opportunity to perform these studies.

Although the results of this study are not of direct benefit to the participating children, it can be expected that more measles outbreaks may occur in this community in the future. Moreover, it will require years before potential plans to achieve global eradication of measles can be implemented. Therefore, a better understanding of the pathogenesis of

measles immune suppression will help in developing new intervention and treatment plans.

### **7.5 Compensation for injury**

The sponsor/investigator has a liability insurance which is in accordance with article 7, subsection 6 of the WMO.

The sponsor (also) has an insurance which is in accordance with the legal requirements in the Netherlands (Article 7 WMO and the Measure regarding Compulsory Insurance for Clinical Research in Humans of 23th June 2003). This insurance provides cover for damage to research subjects through injury or death caused by the study.

1. € 450.000,-- (i.e. four hundred and fifty thousand Euro) for death or injury for each subject who participates in the Research;
2. € 3.500.000,-- (i.e. three million five hundred thousand Euro) for death or injury for all subjects who participate in the Research;
3. € 5.000.000,-- (i.e. five million Euro) for the total damage incurred by the organisation for all damage disclosed by scientific research for the Sponsor as 'verrichter' in the meaning of said Act in each year of insurance coverage.

The insurance applies to the damage that becomes apparent during the study or within 4 years after the end of the study.

### **7.6 Incentives (if applicable)**

Parents of children will not receive an incentive to participate in the study. However, every child that fully participates in the study protocol will be provided with a gift certificate with a value of 10 euro to thank them for their contribution.

## **8. ADMINISTRATIVE ASPECTS, MONITORING AND PUBLICATION**

### **8.1 Handling and storage of data and documents**

Data and materials will be labelled with an identification code. The key to that code will initially be safeguarded by the main investigator and will be transferred to an independent person to be kept for a longer period of time after initial processing of the data and materials. Handling of personal data will comply with the Dutch Personal Data Protection Act.

All clinical specimens that are stored will only contain the identification code, and will never contain names, initials or date of birth. Data tracking will be safeguarded by recording all stored samples in a digital freezer archive which is stored on a secured networkdrive of Erasmus MC. All samples belonging to this study will be made traceable by adding the keyword for the study (Bb2013) to each record.

The study does not involve detailed questionnaires. The only information recorded for subjects recruited to cohort A will be date of sampling, gender, age (in months), number of siblings and number of days before or after onset of rash. The only information recorded for subjects recruited to cohort B will be date of sample collection, date of onset of disease, gender, age (in months) and number of siblings.

### **8.2 Monitoring and Quality Assurance**

A data monitoring plan has been developed to implement quality assurance. In this document, the risk classification is assessed as being negligible. Therefore, data monitoring will be performed as specified in appendix A of the monitoring plan. This requires that the study is visited at least once a year by an independent monitor, who will assess the completeness and integrity of the dossier, the samples and the data as specified in the relevant appendix.

### **8.3 Amendments**

Amendments are changes made to the research after a favourable opinion by the accredited METC has been given. All amendments will be notified to the METC that gave a favourable opinion.

**8.4 Annual progress report**

The sponsor/investigator will submit a summary of the progress of the trial to the accredited METC once a year. Information will be provided on the date of inclusion of the first subject, numbers of subjects included and numbers of subjects that have completed the trial, serious adverse events/ serious adverse reactions, other problems, and amendments.

**8.5 End of study report**

The investigator will notify the accredited METC of the end of the study within a period of 8 weeks. The end of the study is defined as the last patient's last visit.

In case the study is ended prematurely, the investigator will notify the accredited METC within 15 days, including the reasons for the premature termination.

Within one year after the end of the study, the investigator/sponsor will submit a final study report with the results of the study, including any publications/abstracts of the study, to the accredited METC.

**8.6 Public disclosure and publication policy**

Once the research is completed, a summary of the results and/or any scientific publications will be filed with the assessing review committee. We will strictly adhere to the CCMO publication policy. The trial will be registered in a public trial registry before inclusion of the first patient.

